# Health Education Through a Campaign and mHealth to Enhance Knowledge and Quality of Life Among Patients With Chronic Kidney Disease in Bangladesh: Protocol for a Randomized Controlled Trial

**DOI:** 10.2196/30191

**Published:** 2021-11-19

**Keywords:** chronic kidney disease, campaign, mHealth, knowledge, Bangladesh

## Abstract

**Background:**

Despite the growing burden of chronic kidney disease (CKD), disease knowledge and understanding are still lacking, especially in Bangladesh.

**Objective:**

The aim of this study was to evaluate the outcome of a health education intervention in order to enhance knowledge, health-related quality of life (QOL), and motivation regarding healthy lifestyles among rural and periurban adults suffering from CKD.

**Methods:**

A parallel-group (1:1) randomized controlled trial is ongoing in the Mirzapur subdistrict, Bangladesh, where two groups of patients with CKD are being compared. Patients aged 18 years and over with CKD (stages 1-3) were enrolled in November 2020. Patients were randomly allocated into either the intervention group (n=63) or the control group (n=63). The control group received usual treatment, while the intervention group received health education through a CKD campaign facilitated by a nephrologist and via mHealth (ie, periodic mobile phone calls) from community health workers. Both groups were followed up for a period of 6 months. The primary endpoint is patients’ increased knowledge measured using the Chronic Kidney Disease Knowledge Questionnaire. The secondary endpoints are improved QOL measured using the standardized EuroQol 5-Dimension 5-Level (EQ-5D-5L) questionnaire as well as improvements in the levels of blood pressure, BMI, serum creatinine, fasting blood sugar, hemoglobin, cholesterol, high-density lipoprotein cholesterol, triglyceride, serum uric acid, blood urea nitrogen, and albumin to creatinine ratio.

**Results:**

Enrollment of participants began in November 2020; the intervention and follow-up were completed in May 2021. We enrolled 126 patients in the study. Patients’ mean ages were 57.97 (SD 15.03) years in the control group and 57.32 (SD 14.37) years in the intervention group. There were 45 out of 63 (71%) females in the control group and 38 out of 63 (60%) females in the intervention group. In addition, there were 38 out of 63 (60%) literate patients in the control group and 33 out of 63 (52%) literate patients in the intervention group.

**Conclusions:**

It is expected that a combined approach, incorporating both a CKD campaign and mHealth, for health education may be an effective tool for increasing knowledge and improving QOL among patients with CKD.

**Trial Registration:**

ClinicalTrials.gov NCT04094831; https://clinicaltrials.gov/ct2/show/NCT04094831

**International Registered Report Identifier (IRRID):**

DERR1-10.2196/30191

## Introduction

### Background

Chronic kidney disease (CKD) is a public health concern worldwide [1] and directly affects the global burden of morbidity and mortality [2]. CKD is associated with substantial financial costs for both patients and health care systems, and low- and middle-income countries (LMIC) have a much higher economic burden of CKD than developed countries [3]. If the stage of CKD advances in patients, the cost of medical treatment increases [4]. In LMIC, most people with kidney failure have insufficient access to lifesaving renal replacement therapy [5]. Diabetes, hypertension, obesity, and aging are the leading associated factors for CKD throughout the world [6]. These comorbidities make patients with CKD more vulnerable to end-stage renal disease (ESRD) [7].

Knowledge and self-management behaviors must be learned and practiced in order to slow the progression of CKD [8]. Studies have documented that knowledge is essential for slowing kidney function advancement through behavior adjustments, such as physical exercise, dietary changes, patient monitoring (eg, blood pressure [BP] and blood glucose), and adherence to medication [9]. Patients with CKD may benefit from knowledge to change their behavior, improve their outcomes, and lower their mortality rates [10]. Considering the increasing prevalence of CKD, only 6% of the general population and 10% of those at high risk are aware of their CKD status in LMIC [11]. This low health literacy and unawareness in the early stage of the disease are ultimately responsible for CKD disease progression [12]. It has been noted, however, that proper CKD knowledge and management as well as mitigation of CKD-related risks may delay the progression to ESRD and other interrelated health consequences [10,13]. However, most of the patient education research regarding CKD has focused on patients with ESRD. A few studies on CKD have been conducted in Bangladesh, where most were prevalence studies based on a hospitalized urban population; however, there has been no such study in rural Bangladesh describing the knowledge of CKD and health-related quality of life (QOL).

In the field of nephrology, both developed and developing countries are still implementing mobile health (mHealth) [14,15]. However, mobile phone call–based health education has great potential to provide CKD knowledge and improve QOL because it relies on basic mobile technology and requires limited literacy or numeracy skills [16]. In countries with minimal or no national health insurance, such as Bangladesh, CKD education in the early stages of the disease could be an integral part of patient management and the reduction of its related risk factors to slow down its progression; the need is greater in rural and periurban areas. Community health workers (CHWs) have the potential to make a significant difference in the community’s well-being as well as in the lives of people living with kidney disease [17]. A nephrologist-facilitated health campaign, on the other hand, has high potential for delivering CKD education. Thus, this study aimed to evaluate the outcome of a health education intervention in order to enhance knowledge, health-related QOL, and motivation about healthy lifestyle among rural and periurban adults suffering from CKD (stages 1-3).

### Hypothesis

We hypothesize that the knowledge and health-related QOL of patients with CKD will be improved by health education provided by a CKD campaign and a mobile phone call–based intervention.

## Methods

### Design

This study is a community-based, single-centered, prospective, open-label, two-arm (1:1), randomized control trial involving patients with CKD and is being conducted in rural and periurban areas of Bangladesh. This study has been designed in accordance with the CONSORT (Consolidated Standards of Reporting Trials) [18] and SPIRIT (Standard Protocol Items: Recommendations for Interventional Trials) guidelines [19]. The study flowchart is shown in Figure 1. The total study duration was planned to be 1 year; however, the intervention started in mid-November 2020 and the follow-up period was 6 months long. The last follow-up was completed in May 2021.

**Figure 1 figure1:**
[figure not shown]
Flowchart of the study.

### Study Site

This study was conducted in the demographic surveillance system (DSS) area of the Mirzapur subdistrict within the Tangail district, which is located about 60 km north of Dhaka, the capital city of Bangladesh. It has a mixed rural and periurban population [20]. The subdistrict has 13 unions—it is the smallest administrative unit—and 219 villages. Among the 10 unions in Mirzapur that comprise the DSS area, three unions—Mirzapur Sadar, Bhatgram, and Gorai—nearest to our sentinel health facility, which is popularly known as Kumudini Hospital, were selected purposively due to budgetary constraints and time limitations. The study participants were required to visit Kumudini Hospital Laboratory for their study-related investigations and had lower travel costs compared to other areas.

### Study Population and Eligibility Criteria

We recruited patients for this study from among the residents of the DSS. Inclusion criteria for enrollment in the study were as follows: aged 18 years and older, either sex, diagnosed with CKD (stages 1-3: estimated glomerular filtration rate=30-59 mL/min/1.73 m^2^ and/or albumin to creatinine ratio [ACR]≥30 mg/g for more than 3 months) [21], had lived steadily in the locality for at least 5 years, had a personal cell phone or access to a shared phone, and had given written informed consent to participate. The following were excluded from the study: individuals who were hospitalized at the time of enrollment; had any known serious illness with questionable prognosis, for example, stage 4 or 5 CKD, malignancy, mental illness, congenital disease, and physical disability, if they had prescriptions; and did not agree to give consent.

### Randomization

A permuted block-randomization technique was performed using a block size of 6 based on a computer-generated random number sequence. An experienced statistician, not involved in the study in any way, prepared the randomization table and placed the study IDs of the patients with CKD, along with their corresponding intervention allocations, into serially numbered sealed envelopes according to the randomization schedule; these corresponded to the serial numbers of the patients with CKD. These envelopes were kept in an office locker. Allocations to intervention and control groups were concealed in identical sealed envelopes that were only to be opened when the study patient was ready for enrollment under the supervision of the principal investigator. This took place after a patient with CKD was recruited to the study, after obtaining voluntary informed written consent and assignment of a study ID.

### Study Activities and Content

During home visits, the CHWs used a Portable Health Clinic (PHC) box with the essential diagnostic equipment for this research; details are described elsewhere [22,23]. At baseline, CHWs performed home visits to obtain written informed consent and to interview the study patients by administering field-tested standardized questionnaires. The questionnaires collected the following data: sociodemographic information, such as age, gender, marital status, religion, occupation, educational background, and income per month; patients’ current medical status, including medication use; patients’ medical history; and patients’ family history (3rd generation), including current and immediate-past medical status. The same information was collected at 3 months and at 6 months, in case of any changes from baseline. To evaluate the level of knowledge, awareness, and QOL on the part of the study patients, the CHWs also administered questionnaires at baseline to collect this data and administered the same questionnaire at 3 months and at 6 months.

CHWs also performed physical examinations at baseline and performed them again at 3 months and at 6 months to measure the following: BP, pulse, height, weight, waist and hip circumferences, and mid–upper arm circumference. However, during baseline measurements, the study patients were advised to visit Kumudini Hospital Laboratory for collection of blood and urine samples to estimate the condition of their kidneys and their related risk factors, such as serum creatinine, fasting blood sugar (FBS), hemoglobin, cholesterol, high-density lipoprotein cholesterol (HDL-c), triglyceride, serum uric acid, blood urea nitrogen (BUN), and ACR. The same laboratory investigations were done at the end of 6 months (Table 1).

**Table 1 table1:** Study activities.

Schedule		Intervention group	Control group
**Baseline sessions**			
	Week 1	Interview Administer questionnaires Laboratory test (blood and urine)	Interview Administer questionnaires Laboratory test (blood and urine)
	Weeks 1 and 2	CKD^a^ health campaign (3-hour lecture and discussion by a nephrologist) Provide health education materials (leaflet, short textbook, recording notebook, and a 5-gram salt measuring spoon) during campaign	Usual care
	Week 3 to month 3	Mobile education: over the telephone once every 2 weeks (5 times) Blood pressure check: once per week	Usual care
**Intermediate sessions**			
	Week 1 of month 4	Interview Administer questionnaires	Interview Administer questionnaires
	Months 4 to 6	Mobile education: over the telephone once every 2 weeks (5 times) Blood pressure check: once per week	Usual care
**Final session**			
	End of month 6	Interview Administer questionnaires Laboratory test (blood and urine)	Interview Administer questionnaires Laboratory test (blood and urine)

^a^CKD: chronic kidney disease.

### Training of CHWs

CHWs obtained written informed consent, performed physical examinations, interviewed the study participants after administering field-tested questionnaires, and provided health education. Training on the overall study procedure for CHWs was provided by the principal investigator. Training included the following: (1) general information about the study (ie, contact information, study overview, structure, and use of technology) and (2) role-specific information (ie, position description, recruitment, informed consent, data collection, use of an electronic database for data entry, proper use of backup paper copies, and self-evaluation form). Competency was assessed by practicing and role-playing in a private office. A nephrologist trained the CHWs, who then provided mHealth education to the study patients.

### Intervention Group

The intervention group received health education through a CKD campaign using mHealth technology.

#### CKD Campaign

During the half-day CKD campaign, health education materials (ie, a leaflet as seen in Multimedia Appendix 1, a short textbook as seen in Multimedia Appendix 2, and a recording notebook) were provided to the study patients. A nephrologist facilitated the health campaign: the contents of the textbook and leaflet were discussed, and patients were taught how to measure salt using the spoon during preparation of their daily meals. The research team have diverse professional backgrounds and have established the content of the CKD textbook and leaflet in the patients’ native language (Bangla), based on the educational materials from the website of the National Kidney Foundation, New York, United States, after receiving permission. Important information related to CKD, such as basics of the kidney and kidney diseases, stages of disease, risk factors, and preventive measures, were used to develop the textbook and leaflet in the patients’ native language (Bangla).

#### mHealth Technology

Basic health education information about CKD was included in the content to be delivered through a mobile phone call to help patients gain knowledge and awareness and to improve their behaviors. Discussion about the basics of kidney diseases, risk factors, and preventive measures of CKD was performed by CHWs over a mobile phone call with the study patients. The patients had the liberty to discuss their health-related issues with the CHWs over a period of 10 minutes (Table 2). A nephrologist trained the CHWs in the provision of mHealth education.

**Table 2 table2:** Content of mobile health (mHealth) education that took place over a 10-minute mobile phone call.

Topic	Content of mHealth education
Kidneys	Kidneys are bean shaped and positioned near the middle of your back on either side of your backbone. Your kidneys are part of the body’s urine system. Kidney functions include the following: Remove waste products from the body Remove drugs from the body Balance the body’s fluids Release hormones that regulate blood pressure Produce an active form of vitamin D that promotes strong and healthy bones Control the production of red blood cells
Major risk factors for kidney disease	Some major risk factors include the following: Diabetes High blood pressure Family history of kidney disease, diabetes, or high blood pressure Age 50 years or older Obesity Long-time use of painkillers, such as aspirin and ibuprofen Chronic kidney infection Kidney stones Smoking
Some ways to protect kidneys	Ways to protect kidneys include the following: Keep blood sugar, blood pressure, and cholesterol under control Lose weight, if needed Eat healthy meals Take all medicines as prescribed Get regular exercise Do not smoke Avoid some over-the-counter medications, such as aspirin or ibuprofen, because they can harm kidneys
Diabetes	Diabetes damages your kidneys. Managing blood sugar level slows kidney damage. Some advice includes the following: Maintain a healthy diet Keep a healthy body weight Perform at least 30 minutes of moderate-intensity physical exercise, 5 days per week Take medication regularly if prescribed Monitor your blood sugar regularly
Hypertension	Getting your blood pressure back to normal can reduce kidney damage, and some blood pressure tablets actually protect your kidneys. Some advice includes the following: Reduce salt intake: excess salt in your body causes your blood pressure to go up; this damages your blood vessels and increases the risk of heart attack and stroke. Please consume 5 g of salt per day or less (1 teaspoon) Check blood pressure at regular intervals. If possible, buy a blood pressure monitor and measure your blood pressure at home. This allows you to keep records of your blood pressure and you can see if it changes over time Take medication regularly if prescribed

#### Blood Pressure Check

The CHWs performed home visits where they checked patients’ BP once per week and continued over the study period.

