### Control Group

The control group received usual care and were followed up over the study period.

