### Conclusions

If our results show an enhancement of the study outcomes among patients with CKD (stages 1-3), we suggest integrating health education via a campaign and mHealth as effective tools at the national level. Further, we can improve patient knowledge and motivate patients with CKD regarding their health practices to improve their QOL.

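### Weekly home blood pressure visits are part of the tested package, but the hypothesis, abstract and conclusions credit only the campaign and phone calls

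*Protocol article*

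**What the plan says.** **What is delivered.** Within the Intervention Group section, the campaign, the mHealth calls and the blood pressure check each have their own subsection. The last of these describes home visits at which community health workers measured "BP once per week and continued over the study period". Table 1 puts the checks in the intervention column only, from week 3 to month 3 and again in months 4 to 6. The entry is the same in both periods: "Mobile education: over the telephone once every 2 weeks (5 times) Blood pressure check: once per week". The control column for those periods shows usual care, and the Control Group section agrees: "The control group received usual care and were followed up over the study period".

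**What both arms share.** Study Activities and Content gives the common schedule: "CHWs also performed physical examinations at baseline and performed them again at 3 months and at 6 months". Blood pressure is among the measurements taken then. It is also a listed secondary outcome under Endpoints.

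**What is credited.** The hypothesis is that knowledge and quality of life "will be improved by health education provided by a CKD campaign and a mobile phone" call-based intervention. The abstract's methods describe a campaign plus mHealth and explain mHealth as periodic phone calls. The abstract's conclusion, the opening sentence of the Intervention Group section and the final Conclusions section name the same two elements. The last says that, if outcomes improve, "we suggest integrating health education via a campaign and mHealth as effective tools at the national level". The Limitations section does not mention the home visits.

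**The concern.** The article describes a package with a weekly face-to-face component in one arm, then states its hypothesis and its intended recommendation for a package without that component. Because the abstract defines mHealth as phone calls, home visits cannot be read into the term.

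What is at stake is the scope of the conclusion. A health system acting on the final recommendation would set up a campaign and a call service and leave out the home visits. The trial does not test that two-part programme, so its result could not be assumed to carry over.

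Blood pressure is the outcome most directly exposed, since the unnamed component consists of checking it. The article itself treats checking as useful: the hypertension row of Table 2 advises patients to have it done at regular intervals. Knowledge and quality of life could be affected too. Community health workers make the visits, give the phone education and administer the questionnaires, in an open-label trial.

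**Working it through.** The plan gives no total for the visits, so there is no stated figure to reproduce. The sample size does not depend on this point. The check has two parts: a comparison of the sections, and a count of contacts.

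**Sections side by side**

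| Place in the protocol article | Campaign | Calls / mHealth | Weekly home BP check |
|---|---|---|---|
| Table 1, intervention column | yes | yes | yes |
| Intervention Group, subsections | yes | yes | yes |
| Intervention Group, opening sentence | yes | yes | not named |
| Abstract, methods and conclusion | yes | yes | not named |
| Hypothesis | yes | yes | not named |
| Final Conclusions | yes | yes | not named |
| Table 1, control column | no | no | no |

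The operational parts of the Methods define a three-part package. The passages that carry the claim name two parts.

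**Count of contacts given only to the intervention arm**

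Inputs from Table 1: checks are weekly from week 3 to the end of month 6; calls number 5 in each of two periods; there is one campaign session with a 3-hour lecture and discussion. The mHealth section gives 10 minutes per call. Assumptions: 6 months is 26 weeks, and every scheduled visit is made.

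- Visits, weeks 3 to 13: 13 − 3 + 1 = 11
- Visits, weeks 14 to 26: 26 − 14 + 1 = 13
- Total visits: 11 + 13 = 24
- Calls: 5 + 5 = 10, or 10 × 10 = 100 minutes
- Campaign sessions: 1
- Share of contacts that are home visits: 24 / (24 + 10 + 1) = 24 / 35 = 69%

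Sensitivity: if only half the visits took place and all calls did, the share is 12 / (12 + 10 + 1) = 12 / 23 = 52%. The unnamed component therefore remains about half or more of the contacts. The length of a visit is not given, so this is a count of contacts and cannot be turned into contact time.

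**What the contrast estimates**

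Let C be the campaign with its materials, M the calls and V the weekly visits. Randomisation compares C + M + V with usual care, and that difference is estimated without confounding. The hypothesis and conclusions speak of C + M versus usual care. The two are equal only if V adds nothing in the presence of C and M. With two arms, the trial has no data to test that.

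**The case against.** The strongest reply is that nothing is hidden. The check has its own subsection and its own lines in Table 1, and a bundled intervention against usual care is an accepted pragmatic design. No sentence says that the intervention was the campaign and calls and nothing else; the summaries may be shorthand. The hypothesis also concerns knowledge and quality of life, not blood pressure, and no educational content is described for the visits, so an effect of them on a knowledge test is possible but not shown. All of this stands. It limits the point to wording and scope but does not remove it, because the shorthand is what the hypothesis tests and what the recommendation would export.

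A reader might infer more, and the documents do not support it:

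- *That the comparison is invalid, or that no effect can be attributed.* It is valid for the package. Only assignment to the parts fails.
- *That the blood pressure comparison is distorted by habituation to readings by familiar staff.* The article does not say that the same worker returns, and community health workers assess controls as well. A count of 27 readings (24 + 3) against 3 is also not established. It would be 25 if the two later assessments coincide with weekly checks. The content of usual care is not described, so only study-scheduled readings can be counted for controls.
- *That blood pressure should become exploratory.* If the effect is defined as that of the package, a blood pressure difference is a legitimate package effect. Endpoints already fixes its measurement at baseline, 3 and 6 months in both arms, and nothing says that weekly readings enter the comparison. Data collection ended in May 2021 and first results were available in July 2021, so a change of endpoint status now would be post hoc.

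**Conclusion.** The point holds as a mismatch between the intervention as delivered and the intervention as credited. The trial can support a claim about campaign, materials, calls and weekly home blood pressure checks together against usual care. It cannot support the two-part claim in the abstract, hypothesis and conclusions, and it cannot tell how much of any effect on knowledge, quality of life or blood pressure comes from the visits.

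The omitted component amounts to about 24 scheduled visits per intervention patient, on the assumptions of 26 weeks and full delivery. The documents give neither the direction nor the size of the visits' own contribution, and none is claimed here.

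**What to change.** 1. Name the weekly home blood pressure checks as a component of the intervention in the abstract, the hypothesis, the opening of the Intervention Group section and the conclusions.
2. Define the estimated effect as campaign + calls + weekly home blood pressure checks versus usual care.
3. Limit the national recommendation in the Conclusions section to that package.
4. Add to the Limitations that effects, those on blood pressure in particular, belong to the package and cannot be assigned to education alone.

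Leave blood pressure as a secondary outcome, analysed at the common assessments already set under Endpoints.

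The cost is text only: no new data and no change to design, endpoints or analysis. With follow-up complete, the same wording can be carried into the results report. The downside is a less simple claim about campaign and mHealth.
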